#### Retention

Because providers will be followed longitudinally several steps have been planned to reduce attrition. First, providers who plan to leave the study within the study period will not be enrolled at baseline. Second, we will discuss with facility and health system leaders in the study sites to reduce rotation and transfer of providers during the study period unless necessary. Third providers will receive an incentive for participation in all implementation and research activities. Attrition is not a concern for women since they will not be followed longitudinally.

### Study outcomes

#### Aim 1: The primary outcome of the study is PCMC to assess the effectiveness of the *CPIPE* intervention on PCMC.

PCMC will be measured with the PCMC scale developed and validated by our team in Kenya and Ghana [60–62]. The PCMC scale is a 30-item scale administered to perinatal women with 3 sub-scales for dignity and respect, communication and autonomy, and supportive care. Items for each scale are summed to create a score, which is standardized to range from 0 to 100, where higher scores indicate more person-centered care.

#### Aim 2: Secondary outcomes to examine the mechanisms of impact of *CPIPE* on PCMC include

provider stress and burnout, bias awareness and mitigation, as well as provider knowledge, self-efficacy, and behaviors. Provider stress and burnout will be measured using the Cohen perceived stress scale [63] and the Shirom-Melamed Burnout measure [64], which we successfully used in Ghana and Kenya with demonstrated good psychometric properties [46, 65]. For implicit and explicit bias, we will use the Bias Awareness and Mitigation in Maternal Health scale [66] and vignettes, developed and tested in our prior research [67]. We will measure provider knowledge, self-efficacy, and behaviors related to stress, bias, and PCMC, using tools developed for the evaluation of the pilot study. Longitudinal provider surveys will be used to collect this data in all study arms at baseline, midline, and endline.

#### Aim 3: Outcomes to Assess the effect of the CPIPE intervention on distal outcomes in our conceptual framework (Fig. 2) include

receipt of timely postnatal care, breastfeeding initiation and exclusivity, postpartum mental well-being, and post-delivery neonatal complications, which we have shown are associated with PCMC [29, 30]. These will be measured using questions on the timing of breastfeeding onset and current breastfeeding practices, the Edinburgh postnatal depression scale [68], and other questions on postpartum and newborn health in the women’s survey. We will also collect facility-level data on coverage indicators and maternal and neonatal morbidity and mortality from facility records. All study outcomes and sample measures are shown in Table 2. As part of all surveys, we will collect data on various covariates shown in Table 2.

**Table 2 Tab2:**
[figure not shown]
Study outcomes, measures, sources, and timing of capture

### Analysis plan

#### Data quality assurance, initial analyses, and missing data

We will use Redcap to perform real-time checks for data quality assurance [69, 70]. We will use frequency tables and measures of central tendency and variability for continuous variables to characterize the sample overall and by randomization group. If the two groups differ significantly at baseline on one or more covariates, we will use methods based on the Rubin causal model (e.g., propensity scores, double-robust estimation) to obtain the desired effect estimates under the counterfactual assumption of balanced groups [71, 72]. We will address incomplete data with direct maximum likelihood (ML) and multiple imputation (MI) [73] because they make the relatively mild assumption that incomplete data arise from a conditionally missing-at-random (MAR) mechanism [74]. Auxiliary variables will be included to help meet the MAR assumption [75]. The proposed analyses will be conducted using STATA. All program code and results will be documented extensively and archived to enable future review, transparency, and results reproducibility.

##### Aim 1

We hypothesize that mothers in the *CPIPE* intervention group will have higher mean PCMC scores than mothers in the control group at 6 months (H1a) and 12 months (H1b) after baseline. To test hypotheses H1a-H1b, in primary analyses we will fit two-level linear mixed models (LMM) to the PCMC score. Each of these two models will include a fixed effect for the study arm with random intercepts for facility ID to account for the clustering of women within health facilities. Because we will compare *CPIPE* to control at 6 months and then repeat the same comparison at 12 months, alpha (α) will be set at 0.05/2 = 0.025 for each of these two planned comparisons. In secondary analyses for Aim 1, we will extend the LMMs for PCMC to include effects for age and SES and their interactions with the intervention group indicator to explore whether the *CPIPE* intervention differentially benefits younger and lower SES women. Sex as a Biological Variable is not applicable: all participants will be biological females.

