#### Data collection

We will collect data at 3 time points in the intervention and control sites: baseline (T1) prior to the intervention start at each facility, midline 6 months post-baseline/intervention start (T2) to assess immediate impact, and endline 12 months after baseline (6 months post-intervention) (T3) to assess sustainability. Survey data will be collected utilizing Redcap programmed tablets. Process data will be collected throughout the study to assess intervention fidelity and implementation using study logs and Redcap. The provider cohort will be followed longitudinally for 12 months following baseline enrollment. The women’s sample will be multiple cross-sections, where data will be collected from 3 different groups of women at the 3 time points. We will use a mixed-methods approach. Quantitative data will be obtained from surveys followed by IDIs to qualitatively explore factors that may influence outcomes. We will also assess intervention fidelity through observations of intervention activities and a review of project logs [58, 59].

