##### Aim 1 Power Analysis:

We used the NCSS PASS [76] module for a two-level multilevel model with a continuous outcome and randomization at the cluster (i.e., health facility) level to compute the minimum detectable effect size estimates for hypotheses H1a-H1b. We assumed power of 0.80, α = 0.025 per comparison, and *N* = 2000 women from 40 facilities. We further assumed ICC = 0.16 based on our previous data [20, 77]. The minimum detectable standardized mean difference was *d* = 0.41, which is between small and medium effect size, suggesting the proposed primary analyses have sufficient power to detect small to medium effects [78].

##### Aim 2

We anticipate that the intervention will positively impact the intermediate outcomes in our conceptual model (Fig. 1), leading to an improvement in PCMC. We thus hypothesize that, following *CPIPE* exposure, intervention providers will have, higher mean scores on provider knowledge (H2a); self-efficacy (H2b); enabling environment (H2c); behavior (H2d), and lower mean scores on work-related psychological effects (stress, burnout, and bias) (H2e) relative to control providers. To test these hypotheses, we will fit three-level LMMs to each intermediate outcome, with fixed effects for study arm, time, and their interaction, random intercepts for facility ID to account for clustering of providers within health facilities, and random intercepts, random slopes, and their covariance for person ID to account for clustering of repeated measurements within providers. We will perform time-averaged comparisons of repeatedly measured post-baseline observations of the key intermediate outcomes across study arms to examine *CPIPE* intervention effects.

In secondary exploratory analyses, we will investigate whether the intermediate outcomes measured for providers at 6 months mediate the relationship between *CPIPE* intervention assignment and PCMC at 12 months. These analyses will be conducted using principles of structural equation modeling (SEM) and causal mediation methods [1]. We will explore whether *sex as a biological variable* differentially affects intervention effects on the provider-level primary analyses by adding a sex main effect and a sex-by-*CPIPE* assignment interaction term to the LMM models. Sex as a biological variable is not applicable to the mediation analyses due to the outcome applying to women only.

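### Propensity-score or doubly robust estimation is triggered by a significant baseline difference, and the article does not say whether the result replaces or supplements the arm-only primary model

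*Protocol article*

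**What the plan says.** The rule stands in the Analysis plan of the protocol article, under data quality assurance, initial analyses and missing data: "If the two groups differ significantly at baseline on one or more covariates, we will use methods based on the Rubin causal model". The methods and their purpose follow: "e.g., propensity scores, double-robust estimation) to obtain the desired effect estimates under the counterfactual assumption of balanced groups". The two methods are examples, so neither is chosen. The rule gives no test level, and one covariate is enough to trigger it.

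Aim 1, in the same Analysis plan, sets the primary analysis without any condition: "in primary analyses we will fit two-level linear mixed models (LMM) to the PCMC score". Its content is also fixed: "Each of these two models will include a fixed effect for the study arm with random intercepts for facility ID". No baseline covariate enters. On the error rate, "alpha (α) will be set at 0.05/2 = 0.025 for each of these two planned comparisons".

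Data collection says of the women's surveys that "data will be collected from 3 different groups of women at the 3 time points". The women compared at baseline therefore supply no 6- or 12-month outcome. Providers, by contrast, are one cohort followed through all three rounds.

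No part of the article calls the triggered analysis a sensitivity analysis, ranks it against the Aim 1 model, or withdraws it.

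**The concern.** The article describes two routes to the treatment effect, and a significance test on baseline data decides whether the second is taken. Three things are wrong with that.

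- **The status is undefined.** If the trigger fires, a reader cannot tell whether H1a and H1b are decided by the arm-only model or by the propensity-score or doubly robust estimate. The stated purpose, obtaining the desired effect estimates, points to replacement.
- **The trigger measures the wrong thing.** Adjustment is worthwhile when a covariate predicts the outcome. A baseline p-value does not measure that. With 20 facilities per arm, a strong predictor can be unbalanced without reaching significance, and an irrelevant covariate can reach it.
- **For Aims 1 and 3 the trigger looks at other women.** Individual propensity scores in the 6- and 12-month samples cannot correct an imbalance seen among the individual baseline women.

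At stake is a primary result whose estimator is settled after the data are seen, with further freedom over method and covariates. For the binary Aim 3 outcomes the estimand may move too. A mixed logistic model gives a facility-conditional effect, while propensity-score methods usually give a marginal one. Aim 3 is exploratory, and for the linear PCMC score this distinction has little force.

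**Working it through.** **1. The plan's own figure.** The article gives no figure for how often the rule would fire. Its Aim 1 figure is a minimum detectable standardised difference of 0.41. The inputs are in the Aim 1 power analysis: "We assumed power of 0.80, α = 0.025 per comparison", "2000 women from 40 facilities" (50 per facility) and ICC 0.16.

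- Design effect = 1 + (50 − 1) × 0.16 = 8.84
- Detectable difference = (2.241 + 0.842) × √(4 × 8.84 / 2000) = 3.083 × 0.1330 = 0.410

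The figure reproduces with a two-sided 0.025 and no allowance for covariates. It therefore belongs to the arm-only model. The article gives no such figure for the triggered route.

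**2. How often the trigger fires under correct randomisation.** Two inputs are assumptions: k, the number of covariates tested (5 to 20, because Table 2 is not shown), and a valid two-sided 5% test for each.

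For independent covariates, P(at least one significant) = 1 − 0.95^k. For correlated covariates, 200,000 draws of equally correlated normal test statistics were used.

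| Covariates | Independent | Correlation 0.2 | Correlation 0.5 |
|---|---|---|---|
| 5 | 22.6% | 21.8% | 18.2% |
| 10 | 40.1% | 37.7% | 28.6% |
| 20 | 64.2% | 59.1% | 41.9% |

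The range is 18% to 64%.

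**3. Does the two-stage rule inflate type I error?** A null simulation used 40 independent facilities (20 per arm), 20,000 runs per setting and a nominal level of 0.025. Facility-level analysis of covariance on all k covariates stood in for the triggered method. Otherwise the unadjusted comparison was used.

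| Covariates | Outcome variance explained | Trigger fired | Rejection, two-stage rule | Rejection, always adjusted |
|---|---|---|---|---|
| 5 | 0% | 22.9% | 0.0254 | 0.0255 |
| 5 | 30% | 22.6% | 0.0217 | 0.0248 |
| 5 | 60% | 23.0% | 0.0195 | 0.0270 |
| 10 | 0% | 40.3% | 0.0242 | 0.0245 |
| 10 | 30% | 40.5% | 0.0209 | 0.0238 |
| 10 | 60% | 39.8% | 0.0196 | 0.0236 |

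The Monte Carlo standard error is about √(0.025 × 0.975 / 20000) = 0.0011. The two-stage rule is at the nominal level or somewhat below it. Adjusting in every trial stays close to nominal without any trigger.

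**The case against.** The strongest reply is that Aim 1 names the mixed model as primary without qualification, while the conditional rule sits in a general section on initial analyses. A reader might infer that the plan certainly discards the primary model when the trigger fires. The article does not say so. Replacement is the natural reading of the stated purpose, but it is not explicit. What stands is that the rule's status is undefined and nothing marks it as secondary.

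Three other stronger readings are tempting, and the documents do not support them.

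- **The 0.025 level is inflated.** The simulation above gives no sign of it. It tested one fixed stand-in method, so it does not settle every propensity-score or doubly robust choice the rule leaves open, but inflation has not been shown.
- **The trigger would fire almost always, because tests on individual women ignore clustering.** The article describes no such test, and its models for all three aims account for clustering. No figure for that case is used here.
- **The baseline comparison tests a null known to be true and tells nothing.** That is too absolute. Women are identified with the help of providers at the facilities, provider eligibility includes commitment to the intervention training, and the article does not state whether allocation is hidden during baseline recruitment. A difference could therefore reflect recruitment as well as chance. Baseline women also describe their facility's case mix and prior PCMC, and for Aim 2 the baseline providers are the ones analysed. But selective recruitment of women could also arise at 6 and 12 months, where a baseline test cannot see it.

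There is also a fair case for adjusting. In the simulation, when the trigger fired and the covariates were prognostic, the unadjusted test rejected in 0.030 to 0.062 of those trials. That supports adjustment for prognostic covariates. It does not support deciding on adjustment by significance.

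Finally, a covariate list is normally left to the SAP, which is not shown. Its absence is not the point; the point is a data-dependent rule that the article itself states.

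**Conclusion.** The concern holds in limited form. The article makes the choice of a further estimator depend on baseline significance and does not say how the result ranks against the arm-only model. The size is an 18% to 64% chance that the rule fires in a properly randomised trial. That range rests on an assumed 5 to 20 covariates, an assumed valid 5% test for each, and pairwise correlation between 0 and 0.5. The harm is a data-dependent effect estimate and, for exploratory Aim 3, possibly a changed estimand. The remark about different women applies to Aims 1 and 3 only. This should be changed before the outcome data are analysed, but it does not undermine the design.

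**What to change.** Delete the significance trigger. Keep one primary mixed model for each of H1a and H1b, with an adjustment set fixed in advance and applied whatever the baseline table shows:

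- country, as the randomisation stratum;
- facility mean PCMC from the baseline survey;
- women's age and SES, measured in the women analysed.

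All are already available: the strata are fixed by design, PCMC is surveyed at baseline, and age and SES already enter the secondary Aim 1 models. Keep any propensity-score or doubly robust estimate as a labelled sensitivity analysis, with the method named, that does not decide H1a or H1b.

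The cost is a change of wording, with no new data. Country and facility baseline PCMC use two cluster-level degrees of freedom, taking 40 − 2 = 38 to 36 if facilities are counted as the units. The number is smaller if sub-counties or districts are counted, since randomisation is at that level. There is also slightly more analysis work.

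### The primary PCMC models are valid but omit the facility baseline PCMC the trial collects; a prespecified baseline term would gain precision, by an amount that depends on an unstated facility autocorrelation

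*Protocol article*

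**What the plan says.** All references are to the Protocol article.

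- **Hypotheses (Analysis plan, Aim 1).** Mothers in the "intervention group will have higher mean PCMC scores than mothers in the control group at 6 months (H1a) and 12 months (H1b) after baseline".
- **Model (same section).** "To test hypotheses H1a-H1b, in primary analyses we will fit two-level linear mixed models (LMM) to the PCMC score", and "Each of these two models will include a fixed effect for the study arm with random intercepts for facility ID". No baseline PCMC term and no time term is named. The secondary Aim 1 models add age, SES and their interactions with arm, again without baseline PCMC.
- **Alpha (same section).** "0.05/2 = 0.025 for each of these two planned comparisons".
- **Power (Aim 1 Power Analysis).** "We assumed power of 0.80", with "2000 women from 40 facilities" and an ICC of 0.16. "The minimum detectable standardized mean difference was" 0.41.
- **Baseline data (Abstract, Data collection, Sample size).** PCMC is surveyed before the intervention starts in about 2000 women, one third of the 6000, in the same 40 facilities. The women's "sample will be multiple cross-sections, where data will be collected from 3 different groups of women at the 3 time points".
- **Baseline handling (Data quality assurance, initial analyses, and missing data).** If the arms differ significantly at baseline on one or more covariates, propensity-score, double-robust or similar methods will be used.
- **Contrast with Aim 2.** The provider models do include time and an arm-by-time term.

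**The concern.** Because different women are interviewed in each round, no woman has her own baseline. The facilities are the same throughout, so each has a pre-intervention mean PCMC that can serve as a facility-level covariate. With an ICC of 0.16 and about 50 women per facility, most of the variance of a facility mean at any one round lies between facilities. To the extent that those differences persist, baseline can remove them from the error term.

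Two things are at stake. One is precision on the primary outcome, obtainable without interviewing any more women. The other is protection against chance imbalance between 20 and 20 facilities. The significance-triggered clause protects only against imbalances large enough to reach significance, and it makes the choice of primary estimator depend on the data.

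**Working it through.** **Inputs from the document:** 40 facilities, 20 per arm; 2000 women per round, so m = 50 per facility on average and 1000 per arm; ICC = 0.16; alpha = 0.025 per comparison; power 0.80. Sidedness is not stated; two-sided reproduces the plan's figure.

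**Assumed input:** the correlation of true facility means between baseline and follow-up (cluster autocorrelation, CAC). The document gives no value, so a range is shown.

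**Step 1, the plan's own figure.**
- Design effect = 1 + 49 × 0.16 = 8.84.
- SE of the arm difference = sqrt(2 × 8.84 / 1000) = 0.133 SD.
- Minimum detectable effect (MDE) = (2.241 + 0.842) × 0.133 = 0.41.

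This matches, so the stated power takes no credit for baseline.

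**Step 2, what baseline could explain.** The between-facility share of the variance of a facility mean is m × ICC / design effect = 8 / 8.84 = 0.905. This is the share at a single round. It includes facility differences that change over time, so only the part set by the CAC can be removed.

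**Step 3, gain from adjustment.** The correlation of observed facility means is r = 0.905 × CAC. Adjusted variance = (1 − r²) × unadjusted variance, and MDE = 0.41 × sqrt(1 − r²).

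| Assumed CAC | r | 1 − r² | Variance cut | MDE | Power at d = 0.41 |
|---|---|---|---|---|---|
| none used | – | 1 | – | 0.41 | 80% |
| 0.3 | 0.271 | 0.926 | 7% | 0.395 | 83% |
| 0.5 | 0.452 | 0.795 | 20% | 0.366 | 89% |
| 0.7 | 0.633 | 0.599 | 40% | 0.317 | 96% |
| 0.8 | 0.724 | 0.476 | 52% | 0.283 | 99% |

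A simulation of facility-mean ANCOVA (40 facilities, 10,000 runs) gave variance ratios of 0.81 at CAC 0.5 and 0.48 at CAC 0.8, close to the formula. With a noncentral t in place of the normal approximation, the starting MDE is 0.424 (38 df). The adjusted values (37 df) are 0.409, 0.379, 0.328 and 0.293, so the pattern is the same.

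**Step 4, what the conditional clause leaves.** Suppose baseline PCMC counts as a covariate and significance means a two-sided 5% test; the document states neither. The baseline arm difference has the same SE of 0.133, so differences up to 1.96 × 0.133 = 0.26 SD would not trigger adjustment. That is 0.26 / 0.41 = 63% of the MDE. At CAC 0.7 the fraction expected to carry into follow-up is r = 0.633, or 0.633 × 0.26 = 0.16 SD.

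**Step 5, difference-in-differences.** Its variance factor relative to the post-only comparison is 2 × (1 − r). At CAC 0.5 this is 2 × (1 − 0.452) = 1.10, which is worse than ignoring baseline. It breaks even at r = 0.5, that is CAC = 0.5 / 0.905 = 0.55.

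**Step 6, H3a/H3b.** With the stated ICC of 0.039, the between-facility share is 1.95 / 2.911 = 0.67. At CAC 0.3, 0.5 and 0.7, r is 0.20, 0.335 and 0.47, and the variance cut is about 4%, 11% and 22%. This carries the continuous-outcome formula over as an approximation.

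**The case against.** The strongest reply is that nothing here is stated wrongly. A post-only comparison of randomised clusters is valid, the power calculation matches that model, and the trial reaches its declared 80% without baseline. That stands. A reader might infer that the trial is underpowered or that 0.41 is miscalculated; the reproduction in Step 1 rules out the second, and nothing in this point supports the first.

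A second reply is that the article condenses the plan. It does not say that arm is the only fixed effect, and it also omits country, by which allocation was stratified. This has some weight. But the paragraph is labelled as the primary analysis, is specific about its terms, and is powered without a baseline term, so it reads as a chosen model.

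Third, a reader might infer that a large share of precision is certainly being lost, because 90% of the variance of a facility mean lies between facilities. The document does not support this. The 90% describes one round, and how much of it is stable is exactly what the CAC measures. Below a CAC of about 0.4 the gain is small (13% of variance or less); it becomes large only from about 0.6.

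Fourth, it would be wrong to say that the plan ignores baseline imbalance altogether, because the conditional clause exists. It is not a substitute for a prespecified term, for the reason in Step 4.

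Finally, randomisation is at sub-county/district level (Randomization section), so there may be fewer than 40 independent units. The absolute MDEs would then be larger with or without adjustment, and a lost degree of freedom would cost somewhat more.

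**Conclusion.** The concern holds as a matter of efficiency and prespecification, not of validity. The primary H1a/H1b models are sound and 0.41 is correct, but the baseline PCMC survey contributes to neither. Prespecified facility-level adjustment would reduce variance by about 7% to 52% over assumed CACs of 0.3 to 0.8, taking the MDE from 0.41 to between about 0.395 and 0.28. These figures rest on the assumed CAC, the stated ICC of 0.16, 50 women in every facility, a normal approximation and 40 independent facilities. The existence of a gain is well founded; its size cannot be fixed from the document. The change is worth making because the data are already planned and the downside is small.

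**What to change.** State in the analysis plan that both H1 models include the facility's baseline mean PCMC as a facility-level fixed covariate. An alternative is one joint model of all three rounds, with baseline arm means constrained equal, arm effects at 6 and 12 months, and random facility and facility-by-time effects. Do not use a plain difference-in-differences, which loses precision when the CAC is below about 0.55. Name the chosen model as primary, keep the unadjusted model as a sensitivity analysis, and do not let a baseline significance test decide the primary estimator.

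The cost is a sentence in the plan, one model term and about one degree of freedom out of 38, or out of fewer if sub-county/district allocation reduces the number of independent units. No further data are needed. The same adjustment for the exploratory H3a/H3b models, using the facility's baseline proportion, is optional and gains less.

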### Randomization

Randomizing individual providers is not ideal because of a high potential for contamination within facilities and goal of changing facility culture. A cluster RCT design allows us to address threats to internal validity and account for natural clustering of providers within facilities [57]. Forty facilities will be randomized to intervention (*N* = 20) and control (*N* = 20), with arms stratified by country(10 intervention and 10 control facilities in each country). To reduce the risk of contamination due to interaction of providers within the same sub-counties and districts, randomization will be at the sub-county/district level such that control and intervention facilities are not in the same sub-county/district. The facility randomization will be done by a statistician not directly involved in the study. The intervention group will receive all strategies of the *CPIPE* intervention strategies over a period of 6 months after the baseline data collection. At the end of the 6-month implementation, we will collect midline data. Facilities will then be encouraged to continue with the intervention activities without involvement of the study for an additional 6 months, with final data collection at 12 months (endline). The control group will not receive the CPIPE intervention during the 12-month data collection period but will maintain their usual facility level activities. We plan to implement the intervention in the control sites after the endline data collection (assuming preliminary effectiveness). The protocol complies with the standard protocol items for cluster randomized trials. The study design, outcomes, and participant flow are summarized in Figs. 2 and 3.

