### Timeline

The CPIPE trial will be completed over a 5-year period. We will use the first 6 months for study preparation activities, including finalizing the protocol and data collection tools, updating the curriculum with lessons learned from the pilot, and obtaining ethical and other regulatory approvals at UCSF and all sites. We will implement the intervention in 2 blocks in each country, with 10 facilities (5 intervention and 5 control) in each block. Baseline data collection for the first block will start in Y1Q3, followed by intervention implementation, midline, and endline over a period of about one and a half years. Baseline and intervention activities in the next block will start in about Y2 following the same approach in the next year. In year 3 we will offer the intervention to the control groups. Data collection across all sites is anticipated to be completed in Y4. Data cleaning, quality assessment, and preliminary analysis will occur as data are being collected. In year 5, we will continue with data analysis and preparation of manuscripts and presentations, with dissemination in Ghana, Kenya and globally.

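### Allocation is stratified by country, but the primary PCMC models leave country out, so any Kenya–Ghana difference enlarges the standard error and costs power

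*Protocol article*

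**What the plan says.** The Randomization section assigns 20 facilities to each arm, "with arms stratified by country(10 intervention and 10 control facilities in each country". The Timeline section adds: "We will implement the intervention in 2 blocks in each country, with 10 facilities (5 intervention and 5 control) in each block".

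The Analysis plan (Aim 1) tests H1a (6 months) and H1b (12 months) with two separate linear mixed models. Their fixed part is stated as "Each of these two models will include a fixed effect for the study arm" and their random part as "with random intercepts for facility ID to account for the clustering of women within health facilities". Neither country nor block is named.

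The secondary Aim 1 models do not bring country in either: "we will extend the LMMs for PCMC to include effects for age and SES and their interactions with the intervention group indicator". The Aim 2 models have arm, time and their interaction as fixed effects. The Aim 3 models have arm only. The Aim 1 Power Analysis describes a two-level model with no country term, 2000 women in 40 facilities, ICC 0.16, α = 0.025 and power 0.80, giving d = 0.41.

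**The concern.** When allocation is balanced within a stratum, the stratum difference cancels from the arm contrast. The true sampling variance of the contrast is then the within-stratum variance only. A model without the stratum does not know this. It treats the stratum difference as random variation between facilities and adds it to the standard error.

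Here the stratum is country, and the two countries may well differ in mean PCMC. With 40 clusters and alpha split into two tests at 0.025, precision at cluster level is scarce, so an avoidable loss in the primary test matters.

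The plan's one route to further adjustment is triggered when the arms differ significantly on baseline covariates. It would not bring country in, because country is balanced at 10 and 10 facilities per arm.

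**Working it through.** **Inputs from the protocol:** 40 facilities, 20 per arm and 10 per arm in each country; 2000 women per time point, so 50 per facility; ICC 0.16; α = 0.025; power 0.80; d = 0.41. The total SD is set to 1.

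**Assumed, not in the protocol:** the Kenya–Ghana difference D in mean PCMC, in SD units. Like the protocol's own power calculation, the check treats facilities as independently allocated.

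**Step 1: reproduce the stated figure.**
- Variance of a facility mean: 0.16 + 0.84/50 = 0.1768.
- SE of the arm effect: √(4 × 0.1768/40) = 0.133.
- Minimum detectable difference, two-sided α = 0.025: (2.241 + 0.842) × 0.133 = 0.41. This matches the protocol.

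**Step 2: effect of leaving country out.** With half the facilities in each country, each country mean lies D/2 from the overall mean. Country adds 40 × D²/4 to the residual sum of squares, which the arm-only model spreads over 38 degrees of freedom. The estimated variance of a facility mean therefore rises by (D²/4) × (40/38). The true SE is unchanged.

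Power of the arm-only model = Φ((0.41 − 2.241 × reported SE)/true SE).

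**Step 3, case A: 0.16 is the ICC within country.** Worked example at D = 0.5: added variance 0.0625 × 40/38 = 0.0658; reported SE √(4 × 0.2426/40) = 0.1558; ratio to the true SE 0.1558/0.133 = 1.17; power Φ((0.41 − 2.241 × 0.1558)/0.133) = 68%.

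| D (SD) | Reported SE / true SE | Power, arm only | Power, with country |
|---|---|---|---|
| 0 | 1.00 | 80.0% | 80.0% |
| 0.2 | 1.03 | 78.1% | 80.0% |
| 0.3 | 1.065 | 75.7% | 80.0% |
| 0.4 | 1.11 | 72.2% | 80.0% |
| 0.5 | 1.17 | 67.7% | 80.0% |

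**Step 4, case B: 0.16 already includes variation between countries.** Let s be the share of the 0.16 that is due to country. The true facility-mean variance is 0.16(1 − s) + 0.84/50, and the arm-only model adds 0.16 s × 40/38. At s = 0.25 the true variance is 0.12 + 0.0168 = 0.1368 (SE 0.117), and the reported variance is 0.1368 + 0.0421 = 0.1789 (SE 0.134).

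| Country share of facility variance | Power, arm only | Power, with country |
|---|---|---|
| 10% | 81.0% | 83.9% |
| 25% | 82.7% | 89.7% |
| 50% | 86.5% | 97.3% |

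**Step 5: simulation check.** Facility means were simulated under case A (100,000 runs per scenario), with a t reference distribution and true effect 0.41. At D = 0.4, power was 68.6% arm-only against 76.9% with country. At D = 0.5 it was 63.8% against 76.9%. At D = 0 it was 76.9% against 76.7%, so the price of an unneeded country term is negligible. The levels are lower than in Step 3 because the t distribution replaces the normal; the pattern is the same.

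**The case against.** **The article is condensed and an SAP may add the strata.** This is fair as far as it goes: saying that a model will include an arm effect does not exclude other terms. But the Aim 1 text gives both the fixed and the random part of the confirmatory model, and names age and SES as the later additions. As published, the model does not match the stated allocation.

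**The loss may be small.** This stands. No Kenya–Ghana difference is given. Below 0.2 SD the loss is under two percentage points, and at zero it is nil.

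**Stronger readings that the documents do not support.**
- A reader might infer that the trial has less than its stated 80% power. That needs 0.16 to be a within-country ICC. The power section says only that it rests on previous data. In case B the 80% is met.
- A reader might infer that the primary test is conservative overall. The same Randomization section says that "randomization will be at the sub-county/district level such that control and intervention facilities are not in the same sub-county/district". If facilities in one sub-county or district share an arm and are correlated, a facility intercept alone can make the SE too small. The two effects act in opposite directions, so the net size of the test cannot be stated.
- A reader might infer four design strata, country by block. The only stratum named for allocation is country. The 5/5 split stands in the Timeline as an implementation schedule, and no text says that allocation was restricted within block.

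**Aims 2 and 3 were not quantified.** This stands. Their planning ICCs differ (0.15 and 0.039) and Aim 3 is exploratory. The mismatch with the design is the same, but no size is claimed.

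**Conclusion.** The point holds as one of efficiency. The primary models omit the one factor by which allocation is stated to be stratified. The estimate is not biased. Through this component the model-based SE is larger than it needs to be whenever the countries differ in mean PCMC.

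If 0.16 is a within-country ICC, the cost at d = 0.41 runs from nothing (no country difference) through about 4 points (0.3 SD) to about 12 points (0.5 SD). If 0.16 already contains country variation, the planned power is kept, and what is lost is extra power: about 7 points when country is 25% of the facility variance. Both the country difference and the meaning of the ICC are assumptions. The figures isolate this component and say nothing about the effect of district-level allocation.

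**What to change.** Add a fixed effect for country to the H1a and H1b models, and likewise to the Aim 2 linear mixed models and the Aim 3 generalised linear mixed models. Add block within country only if allocation was in fact balanced by block, and say in the Randomization section whether it was. State in the power section whether ICC 0.16 is within-country or pooled over countries.

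The country term costs about one cluster-level degree of freedom (38 to 37, counting facilities) and a line of model wording. It needs no new data and should be fixed before outcome data are analysed by arm. The sub-county or district level of randomisation needs its own treatment, which a country term does not supply.
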